
Generally, methodologically sound studies on the impact of volunteer family support programs are limited, and findings are generally inconsistent due to differences in study methodologies, outcomes examined and characteristics of the programs investigated. Results of meta-analyses and systematic reviews support this by showing varying effect sizes and directions of effects depending on included studies and outcomes of interest [47–49]. Despite inconsistent results, family support programs carried out by volunteers are still continuously being developed and implemented. However, there is a need for ongoing systematic and rigorous evaluations to document the effectiveness of these interventions. The current study is a prospective quasi-experimental trial contributing to this evidence-base. The trial aims to assess the effectiveness of the volunteer intervention Family Club Denmark (FCD) on parent stress, mental health, development, and well-being of parents and children. We will also examine the implementation of FCD concept across organizations, the experience of volunteering within FCD, and the experiences of the participants. The hypothesis is that families in the FCD group will improve more than the control group on all outcomes.

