## Methods and design

The study is a prospective quasi-experimental trial with two conditions: (1) intervention group participating in Family Club Denmark and (2) wait-list control group. The trial aims to examine the effectiveness of Family Club Denmark. The primary outcome of the study is mental well-being and secondary outcomes comprise parenting behavior, parenting stress, self-efficacy and self-worth, family routines, and child well-being. Participants will be allocated to the intervention group primarily after a first-come-first-serve principle. When the maximum number of participants in a specific family club is reached, any further families will join the wait-list and be offered participation after 6 months if a family club exists in the area they live in. The control group will also include families who sign up for a family club in an area where a family club does not yet exist. The study takes place in all five different regions of Denmark. Recruitment commenced in September 2018 and is planned to close in early 2020. We will recruit participants from family clubs starting in fall 2018, spring and fall 2019, and spring 2020. The FCD project is a collaboration between the three third sector partner organizations; KFUMs Sociale Arbejde, FDF, and KFUM Spejderne.

Participants will receive written information on the project and will give electronic written consent to participate in the trial. Ethical approval has been obtained from the internal review board at VIVE. According to Danish law, the project does not need to obtain approval from The Danish National Committee on Health Research Ethics. The protocol conforms to the Standard Protocol Items: Recommendations for Interventional Trials (SPIRIT) guidelines (Fig. 1). The final reports of the trial will be written following the Consolidated Standards of Reporting Trials (CONSORT) statement.

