#### Secondary outcomes

The secondary outcomes include the following measures. It was important to both covers a relatively broad area of outcomes that we believe potentially can be impacted by the intervention but also keep the questionnaire relatively short. Therefore, we have shortened some of the included measures.

**Parent Behavior Inventory (PBI)** is a 20-item measure of parenting behavior of parents of early school-aged children. The PBI includes two subscales with high internal consistency: Supportive/engaged (α = .83) and hostile/coercive (α = .81). The PBI has adequate test-retest reliability (r = .69–.74) in an ethnically diverse sample of mothers. To reduce the total number of items we include 10 items – 5 from each of the two subscales; items 6, 10, 11, 12, 14 for Supportive/Engaged, and items 5, 9, 15, 17, 20 for Hostile/Coercive. The score range is 0–25 for each subscale. A high score is better for Supportive/Engaged, a low score is better for Hostile/Coercive [52]. Cronbach’s alpha is 0.66 for the supportive/engaged subscale and 0.55 for the hostile/coercive subscale in a subsample of the included families.

**The Parenting Stress Scale (PSS)** is an 18-item measure of parenting stress that is rated on a five-point scale (Strongly disagree, Disagree, Undecided, Agree, Strongly Agree). We use the revised Danish version with 16 items where the original items 2 and 11 are left out. The Danish version consists of two subscales: Parental Stress (9 items) and Lack of Parental Satisfaction (7 items). Responses are reversed for the lack of parental satisfaction items and all responses for all items are dichotomized (0–1) before scoring. Total score range 0–9 (Parental Stress subscale) and 0–7 (Lack of Parental Stress subscale). A low score is better for both subscales [53]. Cronbach’s alpha is 0.76 for the parental stress subscale and 0.82 for the lack of parental stress scale in a subsample of the included families.

**The general self-efficacy scale (GSE)** is a 10-item measure of optimistic self-beliefs to cope with a variety of difficult demands in life. To reduce the total number of items we include 3 items (8, 9, and 10). The score range is 3–12 and a high score is better. Cronbach’s alpha for the 3-item version is 0.87 in a subsample of the included families.

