### Statistical analysis

We analyze the primary and secondary outcomes at post-intervention (T2) and follow-up (T3). We use linear regression for normally distributed outcomes and apply robust standard errors to correct for the correlation between observations participating in the same FCD group. In the case of heavily skewed data, we use non-parametric rank-based tests. To check whether the first-come-first-served principle or the allocation of vulnerable families conducted by the volunteers introduce imbalances in the allocation to FCD and the waitlist control, we test for statistical differences in observable characteristics of the two groups using t-tests. In the analysis of the effectiveness of FCD, the hypothesis tested for each outcome is that the FCD group will score better than the wait-list control group. We test this hypothesis with a binary variable indicating the intervention group. We include variables measured at baseline with indications of imbalances (*p* < 0.1) as control variables and apply two-sided tests with 0.05 significance levels throughout. As all outcomes represent a different aspect of the expected outcome of the intervention we do not consider multiple testing issues. We analyze primary and secondary endpoints according to an intention-to-treat (ITT) principle and handle missing data with multiple imputations. Parametric imputation models are preferred, but in case of severe non-normality or convergence issues, we use predictive mean matching or other non-parametric options. We include the 12-month outcome data for exploratory analyses but can also be used as tools in secondary analyses of missingness. Exploratory analysis of data from all three measurements (T1 - baseline, T2 - 6 months and T3–12 months) will be carried out using mixed-effect regression and possibly latent growth curve analysis. The purpose is to assess the longer-term effects of the intervention and to understand how the psychosocial characteristics of the families involved develop over time. In addition to the primary analysis, we will perform subgroup analyses to examine potential differences between subsets of participants. Hence, we analyze subgroups according to the following characteristics: vulnerability (vulnerable or non-vulnerable families); family composition (single parents or cohabiting parents); the age of target child (< 8 years old or ≥ 8 years old); partner organization (KFUMs Sociale Arbejde, FDF, or KFUM Spejderne); the number of volunteers in the FCD; and the number of sessions attended (dose).

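### The reason given for setting multiplicity aside does not support it: every outcome is tested at 0.05 at T2 and T3, and the same paragraph calls T3 exploratory

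*Protocol article*

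**What the plan says.** Methods and design names one primary outcome and several secondary domains: "The primary outcome of the study is mental well-being and secondary outcomes comprise parenting behavior, parenting stress, self-efficacy and self-worth, family routines, and child well-being". Background places them all under one expectation: "The hypothesis is that families in the FCD group will improve more than the control group on all outcomes".

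The Statistical analysis section then makes five statements that bear on this point:

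- Timing: "We analyze the primary and secondary outcomes at post-intervention (T2) and follow-up (T3".
- Unit of testing: "the hypothesis tested for each outcome is that the FCD group will score better than the wait-list control group".
- Level: "apply two-sided tests with 0.05 significance levels throughout".
- Multiplicity: "As all outcomes represent a different aspect of the expected outcome of the intervention we do not consider multiple testing issues".
- Status of T3: "We include the 12-month outcome data for exploratory analyses".

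The section also lists six subgroup characteristics. No rule says how many outcomes must succeed, or which one governs the conclusion, before the programme is called effective.

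**The concern.** The article does more than leave multiplicity to a later analysis plan. It takes a decision and gives a reason, and the reason does not carry the decision. Outcomes that capture different aspects tend to be less correlated. For a fixed number of tests, lower correlation raises the chance that at least one is significant by accident. The premise therefore points towards considering multiplicity.

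The status of T3 adds to this. If T3 stands beside T2, as the first sentence of the section has it, the primary outcome is tested twice at 0.05 and the number of secondary tests doubles. If T3 is exploratory, as a later sentence says, neither follows. Both readings are in the text.

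What is at stake is what may be claimed. Allocation is not random, families know their group, and outcomes come from web surveys that the families complete. An isolated secondary p-value below 0.05 could be offered as evidence of effectiveness, and nothing in the plan as worded limits that.

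**Working it through.** **1. The plan's own figure.** Power considerations gives 80 control and 120 intervention families, SMD 0.35, baseline correlation 0.50, alpha 0.05 and power of about 80%. With baseline adjustment the residual SD is √(1 − 0.5²) = 0.866. The standard error is 0.866 × √(1/80 + 1/120) = 0.125, and 0.35/0.125 = 2.80. Power is Φ(2.80 − 1.96) = Φ(0.84) = 80.0%. The figure is reproduced; it applies to one test at 0.05. The article states no familywise error rate.

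**2. Counting scores.** The count is a reconstruction from the Primary outcome and Secondary outcomes sections.

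| Measure | Scores | Running total |
|---|---|---|
| SWEMWBS (primary) | 1 | 1 |
| PBI ("The PBI includes two subscales with high internal consistency") | 2 | 3 |
| PSS, Danish version, two subscales | 2 | 5 |
| Self-efficacy (GSE, 3 items) | 1 | 6 |
| Self-worth | 1 | 7 |
| Family routine: daily routines, family life, meals | 3 | 10 |
| Child well-being: Kidscreen-10 (age 8 or more), other items (younger) | 2 | 12 |

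The three routine subscales appear only where Cronbach's alpha is reported, and the two child measures are age-specific versions of one outcome. Counting each of these domains once gives 12 − 2 − 1 = 9. Other measures in Table 1 and the subgroup tests are not counted.

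**3. Independent tests, all nulls true.** The chance of at least one p<0.05 among k tests is 1 − 0.95^k.

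- SWEMWBS at T2 only: 5%. At T2 and T3: 1 − 0.95² = 9.75%, and less if the two times are positively correlated.
- 9 scores at T2: 1 − 0.95⁹ = 37.0%.
- 11 secondary scores at T2: 1 − 0.95¹¹ = 43.1%.
- 12 scores at T2: 1 − 0.95¹² = 46.0%.
- 24 tests over T2 and T3: 1 − 0.95²⁴ = 70.8%.

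For a false result in favour of FCD only, each test contributes 0.025. This gives 1 − 0.975¹² = 26.2% for 12 tests and 1 − 0.975²⁴ = 45.5% for 24.

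**4. Correlated tests.** The article gives no correlations between outcomes or between T2 and T3, so these are assumptions. The figures come from 200,000 simulated sets of normal test statistics, with equal correlation between outcomes.

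| Setting | Outcome correlation 0.3 | 0.5 | 0.6 |
|---|---|---|---|
| 12 tests at T2, either direction | 39.9% | 31.9% | 27.8% |
| 12 tests at T2, benefit only | 20.5% | 15.9% | 14.0% |
| 24 tests, T2–T3 correlation 0.5, either direction | 60.9% | 50.8% | 45.1% |
| 24 tests, T2–T3 correlation 0.7, either direction | 57.6% | 47.7% | 42.0% |
| 24 tests, T2–T3 correlation 0.5, benefit only | 32.9% | 26.2% | 22.8% |
| 24 tests, T2–T3 correlation 0.7, benefit only | 30.4% | 24.3% | 21.2% |

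Across the 12-test rows the chance falls as correlation rises, from 46% at zero to 28% at 0.6. This is why distinctness of the outcomes cannot justify setting multiplicity aside.

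**5. Expected number of chance findings.** For 11 secondary scores at T2 it is 11 × 0.05 = 0.55. For all 24 tests it is 24 × 0.05 = 1.2.

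**The case against.** The strongest reply is that distinct, pre-specified hypotheses may each be tested at their own level if each supports only its own claim, and that naming one primary outcome is already the usual hierarchy. Much of this stands. SWEMWBS at T2 has a 5% error whatever happens to the other scores, the power calculation concerns the main hypothesis, and the Discussion already expects causal conclusions to be tentative. Adjusting secondary outcomes beside a single primary is, taken alone, a debatable preference.

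It does not rescue the stated reason. The article calls the outcomes aspects of one expected outcome and joins them in one hypothesis. Read literally, that hypothesis is a conjunction. Requiring every outcome to succeed would avoid the inflation, but the plan tests outcome by outcome and states no such rule.

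Three stronger readings are tempting and are not supported:

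- *That the trial carries a 71% risk of a false claim.* This needs all 24 tests to be independent and to count as confirmatory. Several scales cover related parental constructs, T3 repeats the T2 scales, and one sentence already makes T3 exploratory. The figure also counts results in either direction, whereas the hypothesis is one of benefit.
- *That secondary results carry the same weight as the primary.* The article separates primary from secondary throughout. What it lacks is a limit on what the secondary results may support.
- *That one or two chance findings are likely among the T2 secondaries.* The expected number is 0.55. With independent tests, two or more has probability 1 − 0.95¹¹ − 11 × 0.05 × 0.95¹⁰ = about 10%.

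**Conclusion.** The point holds in limited form. The rationale for disregarding multiple testing is unsound, and the article gives T3 two incompatible roles. The primary test at T2 is unaffected. Counting T3 alongside it raises the primary error to at most 9.75%.

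For all scores together, the chance of at least one p<0.05 under complete null conditions is at most 46% at T2 with 12 scores (37% with 9) and at most 71% over both times. Under the assumed outcome correlations of 0.3 to 0.6, and T2–T3 correlations of 0.5 to 0.7, it is about 28–40% and 42–61%. False findings of benefit alone run at about 14–26% for 12 tests and 21–46% for 24, from the strongest assumed correlation to independence. All of these rest on a reconstructed count of scores and on correlations that the article does not report.

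**What to change.** - Delete the sentence that sets multiple testing aside.
- State that SWEMWBS at T2 is the only confirmatory test, at two-sided 0.05.
- Label all T3 and subgroup tests exploratory, and reword the first sentence of Statistical analysis to agree with the later one on 12-month data. This also suits the design, since some wait-list families will have been offered FCD by then.
- List the secondary scores explicitly, treat them at T2 as supportive, and report Holm or Benjamini–Hochberg adjusted p-values beside the unadjusted ones.

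This needs only a change of wording and a little analysis work, with no new data or families. The drawback is that some secondary results will look less favourable. Primary alpha stays at 0.05 and power at 80%. A flat Bonferroni split over 12 tests is not proposed: at 0.05/12 = 0.0042 the primary test's power would fall to 47%.

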
### Blinding

It is not possible to blind participants or volunteers, as everyone will know if they are participating in FCD or are on a wait-list. The data analyst will be blinded to group status.

### Power considerations

We carried out a power analysis in the design phase to assess the statistical power for testing the main hypothesis. As this study is among the first effectiveness studies of a volunteer intervention there is a lack of previous research to guide the power analysis. Two reviews examine the effect of home visiting interventions (including both professional and paraprofessional providers). Nievar et al. found an average effect size of 0.37 [0.21:0.53] on maternal behavior across 60 studies of home-visiting for at-risk families [56]. The average effect size did not differ significantly between studies with professional and paraprofessional home visitors. Filene et al. found an average effect size of 0.23 [0.13:0.33] on parent behaviors and skills [49]. Two randomized studies examine the effects of volunteer parent training programs for parents with children with ADHD or behavior problems. Chacko & Scavenius report effect sizes post-intervention of 0.3 for parental stress, 0.46 for parenting behavior, and 0.65 for parenting competence [40]. Gardner et al. report effect sizes post-intervention of 0.40 for parenting confidence and 0.65 for parenting skills. None of these studies, however, report results on parental well-being.

We expect controls to constitute approximately 80 out of 200 families. For normally distributed outcomes, a sample of 200 participants (80 control and 120 intervention) would yield a statistical power of approx. 80% with a type 1 error rate of 0.05 for an effect size of 0.35 standardized mean difference (SMD) and a correlation between baseline and post-intervention measures of 0.50.

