### Recruitment

We aim to recruit 200 vulnerable families – 80 to wait-list and 120 to FCD. Participants are recruited through the FCD website, by Facebook adds, by municipal social workers, by local social housing employees, and by direct contact with the local FCD volunteers. The three partner organizations have employed project coordinators to find venues, recruit volunteers, recruit families, handle the website and sign-up, and support volunteers. In most cases, the recruitment process is as follows: (1) A family applies for a specific family club through the website and gives consent for VIVE to contact the family; (2) A project coordinator creates a list with participants; (3) The project coordinator allocates participants to intervention or wait-list control; (4) The project coordinator sends contact information and allocation condition to VIVE; (5) The project coordinator informs VIVE about the starting dates of the family clubs; (6) VIVE sends the first questionnaire (including electronic consent to participate) by text-message and e-mail; and (6) The project coordinator informs participants about allocation. Most families are recruited through the FCD website but some are recruited directly at the local site e.g. through an existing scout unit or the local social housing office. In some cases, families will sign up after the FCD has started.

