Other potential limitations relate to methodological as well as practical challenges. A practical challenge concerns the probability of attrition among participants allocated to the control group; if FCD is perceived as an attractive offer, being assigned to the wait-list with the prospect of being offered the intervention in six months might be difficult to accept. Because we are not able to apply strict random allocation comparability between the intervention group and control group cannot be guaranteed and conclusions about causality are expected to be tentative rather than definitive. On the other hand, the study is conducted in a naturalistic setting, which can be regarded as a strength to represent the setting in which FCD is applied.

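### The stated 80% power presumes that baseline is always in the model and that 200 families are independent and fully observed; the analysis section promises none of these

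*Protocol article*

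**What the plan says.** Power considerations takes "a sample of 200 participants (80 control and 120 intervention" families), "for an effect size of 0.35 standardized mean difference (SMD"), and "a correlation between baseline and post-intervention measures of 0.50", and concludes that this "would yield a statistical power of approx. 80% with a type 1 error rate of 0.05". It mentions no design effect and no allowance for loss to follow-up.

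Statistical analysis describes a linear regression with a binary group indicator. Baseline variables become controls when a test of imbalance gives p<0.1. The authors "apply two-sided tests with 0.05 significance levels throughout" and "apply robust standard errors to correct for the correlation between observations participating in the same FCD group". Missing data are multiply imputed. Vulnerability is listed as a subgroup factor, so the main analysis is not confined to vulnerable families.

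Recruitment states: "We aim to recruit 200 vulnerable families", split 80 to wait-list and 120 to the clubs. These are the same numbers as in the power paragraph, which calls them participants. Allocation puts around nine families in a club and aims for two or three of them to be non-vulnerable. The Discussion says: "A practical challenge concerns the probability of attrition among participants allocated to the control group". No ICC and no attrition percentage appears anywhere.

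**The concern.** The power paragraph takes full credit for a baseline correlation of 0.50, which requires baseline SWEMWBS to be in the model every time. The analysis paragraph makes its entry depend on a significance test. That conflict lies within the article and needs no outside figure.

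Two further features that the article itself acknowledges, correlation within clubs and loss of control families, both reduce power and are not counted. Because the recruitment target equals the number in the power calculation, there is no margin to absorb them.

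At stake is how a null result on SWEMWBS is read. If 80% power is taken at face value, a non-significant result looks like fairly good evidence against a 0.35 SD effect, and it would be weaker evidence than that.

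**Working it through.** **Inputs from the article.** n₁ = 120, n₀ = 80, SMD d = 0.35 (SD = 1), baseline correlation r = 0.50, two-sided alpha 0.05 (z = 1.96), about nine families per club of which two or three are non-vulnerable, hence six or seven (6.5) vulnerable families per club.

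**Assumptions, not in the article.** ICC 0.02, 0.05 or 0.10; attrition 20%, either in both arms or in controls only.

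**Formula.** SE = √[v × (DE/n₁ + 1/n₀)], with v = 1 − r² = 0.75 when baseline is in the model and v = 1 when it is not. DE = 1 + (m − 1) × ICC applies to the club arm only. Power = Φ(d/SE − 1.96). Detectable SMD at 80% power = (1.96 + 0.84) × SE.

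**1. The stated figure.** v = 0.75, DE = 1: SE = √[0.75 × (1/120 + 1/80)] = 0.1250; 0.35/0.1250 = 2.80; power 79.96%. It reproduces.

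**2. Baseline not in the model.** v = 1: SE = 0.1443; 0.35/0.1443 = 2.425; power 67.9%. A change score gives the same result, since 2(1 − 0.50) = 1.

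**3. The p<0.1 rule.** Simulated with comparable groups, independent families and no loss (40,000 runs): baseline enters in about 10% of runs and power is 69.5%, against 79.5% when it is always in and 67.8% when it is never in.

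**4. Clustering only, baseline always adjusted, 120 v 80.**

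| ICC | m = 6.5: DE, power, detectable SMD | m = 9: DE, power, detectable SMD |
|---|---|---|
| 0.02 | 1.11, 78%, 0.36 | 1.16, 77%, 0.36 |
| 0.05 | 1.275, 76%, 0.37 | 1.40, 74%, 0.38 |
| 0.10 | 1.55, 72%, 0.39 | 1.80, 68%, 0.40 |

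**5. Attrition of 20% only, baseline always adjusted, observed cases.** Both arms (96 v 64): SE 0.1398, power 71%. Controls only (120 v 64): SE 0.1340, power 74%.

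**6. ICC 0.05 and 20% attrition, baseline always adjusted.** Where both arms lose 20%, the club size shrinks to 0.8m.

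| Loss | m = 6.5 | m = 9 |
|---|---|---|
| Both arms (96 v 64) | DE 1.21, power 67%, SMD 0.41 | DE 1.31, power 66%, SMD 0.42 |
| Controls only (120 v 64) | DE 1.275, power 70%, SMD 0.39 | DE 1.40, power 69%, SMD 0.40 |

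**7. If non-vulnerable families are analysed in addition to the 200.** 120 vulnerable families at seven per club fill 120/7 = 17.1 clubs, or 17.1 × 9 ≈ 154 families. At six per club they fill 20 clubs, or 180 families. With m = 9, ICC 0.05 (DE 1.40), 80 controls, no attrition and baseline in the model, power is 79% for 154 and 81% for 180.

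**The case against.** The strongest reply is that nothing has been miscalculated. The power statement is approximate, dates from the design phase, lists its inputs and reproduces. That is correct, and the point is not an arithmetic slip. The stated inputs do not match the stated analysis.

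It can also be said that the p<0.1 rule may only select additional controls, with adjustment for the baseline outcome implied by the correlation of 0.50, and that a fuller analysis plan may settle this. That is possible, but the analysis paragraph does not say so and its wording covers baseline variables generally. Because allocation is not randomised, imbalance may well be more frequent than chance, so the true figure under the rule could lie above 70%. That stands as a qualification. However, the article itself argues that allocation is close to random given vulnerability and language, and planned power should not depend on imbalance occurring.

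Multiple imputation may recover a little of the attrition loss; the observed-case figures give it no credit. Club-robust standard errors protect the validity of the test, but they do not restore power.

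A reader might infer that the plan's own figures put power at 53% to 74%. The documents do not support that. Both ends need an ICC of 0.05 that the article does not give. The 74% end is clustering alone with nine per club. The 53% end also takes 20% from both arms, although the Discussion raises attrition only for controls, and assumes that baseline is never in the model. Nine per club with only 120 club families is the pessimistic pairing: if the 200 are vulnerable families, six or seven share a club.

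**Conclusion.** The concern holds in a limited form. The 80% belongs to a baseline-adjusted analysis of 200 independent, fully observed families. The analysis as written does not guarantee the adjustment, and the article itself expects departures from the other two conditions.

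The firmest part needs no outside figure: with comparable groups, the p<0.1 rule alone brings power to about 70%, with 68% as the value if baseline never enters. The rest is a sensitivity range on assumed values. With baseline always adjusted, clustering alone gives 68% to 78% over ICC 0.02 to 0.10, 20% attrition alone gives 71% to 74%, and ICC 0.05 with 20% attrition gives 66% to 70%. A small ICC by itself costs only two or three points.

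The size also depends on who the 200 are. If non-vulnerable families are analysed on top of them, the larger club arm roughly offsets clustering at ICC 0.05 when baseline is in the model and nobody is lost. The article does not say which reading applies. A reader might go further and conclude that vulnerable families should form the primary analysis set. That is a separate choice of target population and does not follow from the power calculation.

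**What to change.** 1. State that baseline SWEMWBS is a fixed covariate in the primary model, whatever the imbalance test shows. This brings the analysis into line with the correlation of 0.50 and, with comparable groups, recovers about ten points of power.
2. Restate power for the fixed target of 200, with a design effect in the club arm, a range of ICCs and a range of attrition, each labelled as an assumption. Give power at 0.35 and the detectable SMD (about 0.36 to 0.42 over the ranges above).
3. Say whether the 200 participants under Power considerations are the vulnerable families named under Recruitment or all analysed families, and use the matching club size (six or seven, or nine).

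The cost is a change of text. No extra families are needed, and the stated power becomes somewhat less favourable.

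### The 80% power needs the baseline score in the model, but the analysis admits it only if imbalanced at p < 0.1; as written, power is about 68–69%

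*Protocol article*

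**What the plan says.** The Power considerations section of the protocol article states that "a sample of 200 participants (80 control and 120 intervention) would yield a statistical power of approx. 80" per cent. The significance level behind this is 0.05, and the remaining assumptions are "an effect size of 0.35 standardized mean difference (SMD) and a correlation between baseline and post-intervention measures of 0.50".

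The Statistical analysis section gives linear regression for normally distributed outcomes at T2 and T3, with robust standard errors for families in the same club. On the group comparison it says "We test this hypothesis with a binary variable indicating the intervention group". On covariates it says "We include variables measured at baseline with indications of imbalances", with p < 0.1 as the threshold, and it says that the authors "apply two-sided tests with 0.05 significance levels throughout". It nowhere says that the baseline value of the outcome is always in the model. The mixed-effect and growth-curve models that use all three measurements are labelled exploratory.

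The Outcomes section and Table 1 show that mental well-being is measured at T1, T2 and T3.

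**The concern.** The power calculation and the analysis describe two different models. A baseline-to-follow-up correlation of 0.50 helps only an analysis that uses the baseline score. Read literally, the covariate rule makes baseline SWEMWBS pass through a significance test before it may enter, so in a balanced sample it will usually stay out.

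Two things are at stake. The first is that the primary test may lack the power claimed for it. The second is confounding. The article accepts in its Allocation section that first-come-first-served sign-up may select different families, and in its Discussion that the groups' comparability is not assured. Baseline well-being is the obvious variable to adjust for in such a comparison, and a balance test with limited power is a poor way to decide whether to do so.

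**Working it through.** **Inputs.** From Power considerations: 80 control and 120 intervention families, SMD 0.35 (so SD = 1), r = 0.50, type 1 error 0.05. From Statistical analysis: two-sided tests, and baseline variables included only at p < 0.1. Observations are treated as independent and complete, which is the only basis on which the stated figure reproduces below.

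**Step 1. Reproduce the stated figure (baseline always in the model).**
SE = √[(1 − r²)(1/80 + 1/120)] = √[0.75 × 0.020833] = 0.125.
0.35 / 0.125 = 2.80.
Power = 79.6% (noncentral t) or 80.0% (normal approximation). This matches the plan.

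**Step 2. Baseline left out.**
SE = √(1/80 + 1/120) = 0.1443.
0.35 / 0.1443 = 2.43.
Power = 67.5% (noncentral t) or 67.9% (normal).

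**Step 3. Change score.**
The variance of the change is 2(1 − 0.50) = 1, the same as that of the T2 score, so power is again 67.5%. A change-score analysis does not rescue the figure.

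**Step 4. One-sided variants.**
A one-sided unadjusted test gives 78%, which is near 80%. It contradicts the two-sided tests in the plan and makes no use of r. A one-sided adjusted test gives 87%. Neither explains the stated figure.

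**Step 5. The rule as written, with only chance imbalance at baseline.**
In a simulation of 60,000 trials, a t-test on the baseline score decided whether that score was adjusted for. It entered in 10% of trials. Power under the rule was 69.3%, against 79.6% for always adjusting and 67.4% for never adjusting. With no treatment effect, the rule rejected in about 3.8% of trials, so it does not use the full 5%.

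**Step 6. The rule with a true baseline difference.**
The documents give no figure for this, so differences from −0.4 to +0.4 SD are assumed (30,000 trials each; positive means FCD families start better). Bias is the mean error of the estimated effect.

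| True difference (SD) | Baseline enters | Power under rule | Bias (SD) |
|---|---|---|---|
| −0.4 | 87% | 73% | −0.01 |
| −0.2 | 40% | 63% | −0.03 |
| −0.1 | 18% | 63% | −0.03 |
| 0 | 10% | 70% | 0.00 |
| +0.1 | 18% | 76% | +0.03 |
| +0.2 | 40% | 81% | +0.03 |
| +0.4 | 87% | 79% | +0.01 |

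Where power under the rule exceeds that of always adjusting (78–80%), the excess comes from upward bias. Type 1 error stayed between about 4% and 5.3%.

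**Step 7. What may go unadjusted in one trial.**
The threshold p < 0.1 corresponds to an observed gap of 1.653 × 0.1443 = 0.24 SD. A gap just below it carries 0.50 × 0.24 = 0.12 SD into the T2 contrast, about a third of the target effect (0.12 / 0.35 = 0.34).

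**Step 8. Equivalent costs.**
Without baseline, the effect detectable with 80% power is 0.41 SD (0.40 by the normal approximation), against 0.35 with it. Keeping 0.35 with no baseline adjustment would need about 268 families (107 + 161).

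**The case against.** The strongest reply is that this is a gap in wording. The article never says that the baseline score is excluded. The p < 0.1 rule can be read as governing extra covariates, and the use of r = 0.50 suggests that adjustment was intended. The article condenses a fuller protocol that is not shown. That may well describe the authors' intention, but the published rule covers all baseline variables and makes no exception for the outcome's own baseline. A fuller document that always adjusted would contradict the rule, so the text needs correcting either way.

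A second reply is that low power and confounding call for opposite conditions: baseline stays out most often when the groups are alike, and is admitted more often when they differ. This stands in part. At a true difference of 0.4 SD the score enters in 87% of trials, and the average bias peaks at only about 0.03 SD. But at 0.1 and 0.2 SD it still stays out in 82% and 60% of trials. It also follows that no single power figure applies to a non-randomised comparison. The 68–69% holds under balance, and the range has to be stated.

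Third, the hypothesis in the Background speaks of greater improvement, while the Statistical analysis section tests for a better score. In balanced groups the two contrasts agree, so the wording of the hypothesis adds little here.

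Fourth, the remedy does not suit every outcome automatically. Rank-based tests are planned for heavily skewed data, and child well-being uses different instruments below and from age 8. Both are minor exceptions and do not touch SWEMWBS, unless it proves heavily skewed.

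**Conclusion.** The concern holds. The 80% belongs to an analysis with the baseline score always included, and the article specifies a different one. If the groups are balanced apart from chance, power for an SMD of 0.35 is 67.5% without baseline and about 69% under the p < 0.1 rule, a loss of 10 to 12 percentage points. If the groups truly differ at baseline by up to 0.4 SD, power under the rule lies between about 63% and 81%, with an average bias of up to about 0.03 SD.

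These results assume normal outcomes, r = 0.50 and independent, complete observations. Clustering within clubs and attrition would lower the adjusted and unadjusted figures alike and are separate matters. The rule does not materially inflate false positives; the harm is lost power and avoidable residual confounding. Because it affects the model for the primary test, it should be settled before analysis.

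**What to change.** State that every regression of an outcome at T2 or T3 includes the T1 value of that outcome as a covariate, regardless of any balance test. For the primary outcome this means T2 SWEMWBS on group, T1 SWEMWBS and any other covariates named in advance. If the p < 0.1 rule is kept, confine it to other variables. Carry the same baseline term into the imputation model. Say briefly what is done for outcomes analysed by rank-based tests, and for children whose well-being instrument changes at age 8.

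The cost is a few sentences. SWEMWBS and the other outcomes are already scheduled at T1, so no new data are needed, and the stated 80% is restored on the plan's own assumptions. If the authors prefer to keep the present rule, the power statement should be changed to about 68–69% under balance.
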